## **1.7 Risk/benefits**

There are no known risks to participating in the trial. We assume that participants in the intervention group will benefit from more in depth antenatal classes in small groups, however, we cannot rule out the possibility that the intervention group may experience an increase in worries about issues related to pregnancy and parenting. Participants randomised to the control group may experience some disappointment. The control group will receive standard care why we consider being randomised to the control group as ethically justifiable.

## **1.8 Ethical consideration**

### **1.8.1 Ethical justification**

The Capital region of Denmark aims to implement birth and parent preparation in small groups for all expectant parents. However, it is unknown if antenatal preparation in small groups is superior to standard care, what the classes should encompass, and what the cost-effectiveness of antenatal preparation in small groups is compared to large-scale preparation in auditoriums. In a healthcare system with limited resources it is important to develop an up-to-date research based antenatal preparation program and examine its efficiency and cost-effectiveness prior to implementation, in order to prevent excess obstetric procedures and use of health care, to improve newborn families' quality of life, and to meet the aim of evidence based medicine and most value for money. The project is a large scale, individually randomised trial of an antenatal parenting program addressing determinants of coping with birth, breastfeeding and parenting. The development of a comprehensive, theoretically founded parenting program provides an opportunity to test if antenatal parenting training – in line with the recommendations set forward by the Danish National Board of health - can increase parenting resources, promote short and long-term health and thriving in the child and the family and affect use of healthcare services. We hypothesise that a successful parenting program will increase parental resources, promote healthy parental behaviour, and improve health and thriving for newborn families; however, we do not know if birth and parent preparation in small groups is superior to antenatal classes held in auditoriums, why we believe the intervention to be ethically justifiable. Collaboration with service providers and leading national and international researchers and clinicians in this field has been established. Therefore, this proposed project may substantially improve the current "state-of-the-art".

### **1.8.2 Informed consent**

All participants considered for this trial will be provided with written and oral information on this trial so that participants can make an informed decision about their participation in this trial. A consent form

must be signed by the participant and by the investigator seeking the consent, and participants will be informed of the possibility to withdraw their consent from the trial at any time.

All pregnant women receive a written invitation prior to their first birth clinic visit. Along with this invitation pregnant women will receive written information in form of a pamphlet about the trial. This information will also be available on a project website. At the birth clinic visit (<20th week of gestation) the woman will receive verbal information and give her informed consent or refusal of participation. A project phone line will be established where participants can contact a project member throughout the trial if she has further questions, or wishes to withdraw her consent for participation in the trial.

## **2. Trial objectives and purpose**

The primary aim is to compare parenting resources, health and thriving, and use of healthcare services in newborn families enrolled in a research-based standardised antenatal birth and parenting program in small groups with those allocated to standard care.

Development of the program: We have developed a comprehensive, theoretically founded parenting program in collaboration with midwives, health care visitors, psychologists and family therapists, parents, and leading national and international researchers and clinicians in this field.

Process evaluation:

As the degree of implementation of a program is crucial to its ability to achieve any effect, we also aim to ensure careful implementation of the program, and to conduct a thorough process evaluation highlighting enabling factors and barriers to the implementation. Focus group interviews with service providers, group facilitators and participants will be carried out. Program fidelity e.g. whether the protocol is followed in program delivery, and how much of the intended program the participants are receiving, as well as program reach e.g. what proportions of the intended groups are participating in the program, has an impact on the effect of an intervention (33). These aspects, although very important, are rarely commented on when reporting the effect of an intervention. We will evaluate whether the protocol is followed in program delivery and how much of the intended program the participants are receiving. Participants will be asked to fill in an electronic questionnaire on-site at the end of each session. The questionnaire will highlight whether the intended subjects of the session have been covered as well as to what extent the participants found the information given useful. Group facilitators will be asked to fill in a similar questionnaire with the opportunity to explain why certain topics may have been omitted. Furthermore participant observation will be carried out during random sessions.

Non respondent/non-participation:

What proportions of the intended groups are participating in the program will be explored by examining demographic characteristics of those who declined to participate in the trial via the national registers, as well as examining characteristics of those who accepted and then did or did not show up for the

sessions. Interest and participation in parenting programs is likely only to reach some parents, for instance uptake may be related to socioeconomic position (13, 34). It is possible but unknown if offering a parenting program in small local groups increases the likelihood of participation by parents who may otherwise be difficult to reach.

Cost-effectiveness analysis:

Finally the incremental societal cost of the intervention will be calculated and compared to the measured outcomes in a cost-effectiveness analysis. Direct health care costs as well as productivity costs in terms of labour market participation and sickness absence. For this we will use data from the obstetric database at Hvidovre Hospital, national registers and questionnaires.

### **3. Trial design**

#### **3.1 Trial design**

Individually randomised trial sited at a large birth clinic in the Copenhagen Capital Region, Hvidovre Hospital. Please find an overview of the trial design attached as separate file.

#### **3.2 Randomisation**

Information about women willing to participate in the project will be given to a project employee, who will perform individual web-based randomization according to a computer-generated allocation sequence with a varying block size kept unknown to the investigators, stratified for vulnerability (organized by the Copenhagen Trial Unit). The project employee will subsequently ensure that the birth site invites the selected women and their partners to the first session of the intervention. Women who are randomised to the control group will be sent a standardised letter highlighting the importance of the follow-up. The allocation of participants to the intervention will be 1:1 to the intervention and the control group respectively.

#### **3.3 Trial intervention**

Intervention: The intervention is developed using a systematic framework for health promotion program planners "Planning health promotion programs: an intervention mapping approach" (33). This systematic framework aids effective decision making at each step in intervention planning, implementation, and evaluation (33).

The intervention consists of a research-based general birth and parenting training program. The intervention will have two arms:

- 1) A research-based parenting program based on the recommendations from the National Board of Health and inspired by "Towards Parenthood" (35) and "Prevention and Relationship Enhancement Program" (PREP). The intervention arm is described in more detail below.

2) Standard care (control group). The pregnant woman and her partner are offered two antenatal lectures in an auditorium.

The intervention arm: Groups of approximately 6-7 couples (or mothers) will meet three times during pregnancy and 1 time 5 weeks after expected due date, for the duration of 2.5 hours per session. (The aim is to create groups of 6-7 couples; however, due to fluctuations in uptake groups of 4-9 couples will be deemed acceptable). The sessions will include information and discussions about emotions and expectations related to birth and parenting, identification of social network resources, couple communication, breastfeeding, parent-child attachment, directions on taking care of a newborn, and recognising common signs of mood disorders and how to react. A patient-network website which enables parents to gain further information, communicate with other parents and consult online with a midwife and a health visitor will be created. In addition to gaining knowledge about issues related to birth and parenting, and creating an environment where parents can discuss their feelings and concerns, the program aims at enhancing expectant parents' awareness of their own resources and problem-solving strategies. Furthermore the way the groups are composited will enable participants to establish relations with other expectant parents in their local area. All sessions will be led by a midwife. The postnatal session will be conducted in collaboration with a health visitor, to increase knowledge on available resources in the local communities

### **3.4 Blinding**

It is not possible to blind participants or service providers. Data will be blinded by a data- manager and the investigators and statistician will therefore be blinded to participants' intervention category during data analyses. Participants' intervention category will first be revealed to outcome assessors and investigators after they have drawn conclusions about outcome effects of group X versus Y.

### **3.5 Duration**

Participants will be invited to participate in the trial at their first antenatal visit. The intervention consists of 4 sessions that last for 2,5 hours per session. The first intervention session will take place at 25 weeks gestation, followed by 2 sessions at 33 and 35 weeks of gestation, and a post-natal session 5 weeks after expected due date.

The control group are offered two lectures in an auditorium during pregnancy.

### **3.6 Discontinuation of individual participants**

Participants will be able to withdraw from the trial at any time. Women who have a miscarriage or a stillborn child will be discontinued in the trial. The vice-chief midwife at Hvidovre Hospital will monitor occurrence of late miscarriages, stillbirths, and maternal deaths weekly and keep the project group informed.

### **3.7 Intervention accountability**

---

Intervention development and data-collections are carried out by the Centre for Intervention Research and the National Institute of Public Health with guidance from relevant collaborators. The program will be developed with input from a working group consisting of midwives, health visitors, psychologists and family therapists, and representatives of the general public. Once completed, selected program facilitators from the birth sites will be trained on a workshop in the scope and delivery of the program by members of the working group.

### **3.8 Data collection**

Data will be collected from both parents using web-based questionnaires at: baseline (<20 weeks gestation), 37 weeks gestation, 9 weeks after expected due date, 6 months after expected due date, 1 year after expected due date. Participants will be contacted via e-mail, when due to answer a questionnaire. Two reminders will be sent via additional e-mails, the first after a week and the second after 14 days. Where possible a member of the project group will contact non-respondents by phone a week after the final e-mail reminder.

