## Wordlist and abbreviations

AND Antenatal depression

EPDS Edinburgh Postnatal Depression Scale

Gestation: The gestation period is the time in which a foetus develops, beginning with fertilization and ending at birth

MDI Major Depression Index (MDI)

NIPH National Institute of Public Health

Nulliparous : Never having given birth to a child

PND Postnatal depression

PP post-partum i.e. after birth

PSE Parenting self-efficacy

PSS Perceived stress scale

SOC Sense of coherence

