Central to how parents adapt to parenthood are their perceptions of having access to available resources for meeting the demands of parenthood (2, 11). Some of the most important resources related to parenting are: self-efficacy, social network and support, and parenting alliance (2, 23, 88). The Newborn antenatal education program aims to increase these resources, hence the transition to parenthood should be smoother and less stressful if the program is successful.

*Trust in own ability to cope with birth*

Will be measured using questionnaire data (tp1). Questions are developed for this trial. Structured antenatal education may improve women's trust in their ability to cope with birth resulting in e.g. lower epidural rates (28).

*Trust in own ability to cope at discharge*

Will be measured using questionnaire data (tp1). Questions are developed for this trial. Perceived readiness for discharge has become increasingly important to assess as hospital length of stay following birth has decreased - it may affect patient satisfaction, physical, emotional, psychological, and social outcomes (89).

*Parenting self-efficacy (PSE)*

To evaluate parenting self-efficacy (PSE) i.e. the individual's appraisal of his or her competence in the parenting role Salonen's PSE scale measuring parents' perceived competence in day-to-day infant care tasks, as well as interactive behaviour will be used (tp 2) (90).

High PSE is important for sense of well-being and parenting satisfaction (23, 91). PSE has been identified as an important buffer against parenting stress (23, 88), a major determinant of parenting behaviors, and closely linked to child development outcomes and psychosocial child adjustment (25, 92-94). Experience of childbirth has an impact on PSE (95-97). Findings suggest that parenting programs may improve PSE (98-101). However, studies on PSE around the time of childbirth are scarce (90, 100, 102-104), hardly any are randomised trials, sample sizes are small, and thus generalisability of findings is limited (100, 102).

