## 6.2 Method and timing

**Table 1: Assessment tools and outcome measures**

Baseline is time point 0 (tp0) (<20 weeks gestation), 37 weeks gestation (tp1), 9 weeks (tp2), 6 months (tp3) and 1 year after expected due date (tp4).

| Tools                                                                               | Outcomes                                          | Time points  |
|-------------------------------------------------------------------------------------|---------------------------------------------------|--------------|
| Primary measure                                                                     |                                                   |              |
| Hvidovre hospital obstetric database                                                | Epidural use                                      | • Birth      |
| Secondary Measures                                                                  |                                                   |              |
| Perceived stress scale                                                              | Stress                                            | • 0,1, 2,3,4 |
| Swedish Parenthood Stress Questionnaire (SPSQ) translated into Danish               | Parenting stress                                  | • 2,3,4      |
| The Parenting alliance measure                                                      | Parenting alliance                                | • 3,4        |
| Explorative Measures                                                                |                                                   |              |
| Single item question from the Longitudinal Copenhagen City Heart Study              | Stress frequency                                  | • 0,3,4      |
| Single item question from the Longitudinal Copenhagen City Heart Study              | Stress intensity                                  | • 0,3,4      |
| 10-item Edinburgh Postnatal Depression Scale                                        | Antenatal and Postnatal depressive symptomatology | • 0,1,2      |
| MDI, ICD-10                                                                         | Depressive symptomatology                         | • 3          |
| The Hopkins Symptom Check List (SCL-25) first 10 items (anxiety score, SCL-anxiety) | Anxiety                                           | • 1,2,3      |

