## 7.2 Statistical methods

Reporting will follow the guidelines of the CONSORT-statement. Statistical analyses will be intention to treat as well as per protocol. The level of significance will be 0.05.

The analysis of the primary binary outcome will be done using the generalised linear mixed model with distribution = binomial, link = logit.

If the percent missing cases > 5%, the results of this analysis will be subjected to a 'worst case' and a 'best case' scenario analysis of the potential impact of missing values. Assume a beneficial effect (less use of epidural analgesia) is noted in one group (group A) as compared to the other group (group B). A worst case scenario will then be constructed where missing values in group A are imputed by a "yes" to use of epidural analgesia and missing values in group B are imputed by a "no" to use of epidural analgesia. A corresponding best case scenario will also be constructed and the result under both scenarios will be computed.

Analyses (adjusted by baseline value and protocol specified variables) of perceived stress at 37 week gestation and for each of the other two secondary outcomes of the area under the curve (AUC) from 9 weeks to one year after due date will be done.

If the percent missing cases of an outcome is >5% and p of Little's test (1) < 5%, a number of datasets with observed values and predicted unobserved values necessary to produce an efficiency > 99% will be produced using multiple imputations (SAS version 9.3 or later)(2). The primary analysis will then be that based on these data sets.

Multiplicity will be dealt with as follows: the primary outcome will be tested at the 5% level. The p values of the remaining four tests will be adjusted using Hommel's procedure (Konietschke, 2012). In all events all observed p values will be reported.

For the secondary outcome measure 'Perceived Stress Scale' it will be tested using the general linear univariate model, whether the mean values differ between the two intervention groups at time 1 (37 week gestation), time 2 (9 weeks following birth), time 3 (6 months following birth), and time 4 (12 months following birth).

For the secondary outcome measure 'Swedish Parenthood Stress Questionnaire' it will be tested using the general linear univariate model, whether the mean values differ between the two intervention groups at time 2 (9 weeks following birth), time 3 (6 months following birth), and time 4 (12 months following birth).

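### The 37-week questionnaire (tp1) keeps the general reminder chain to about 40 weeks and is not closed at birth, so some antenatal measures will be answered after delivery

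*Protocol*

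**What the plan says.** Section 3.8 sends the web questionnaires at baseline, 37 weeks gestation, and 9 weeks, 6 months and 1 year after the expected due date. One contact rule covers all five: an e-mail when due, then "Two reminders will be sent via additional e-mails, the first after a week and the second after 14 days". After that, "Where possible a member of the project group will contact non-respondents by phone a week after the final e-mail reminder".

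Three other places bear on tp1:

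- **What gestation means.** The wordlist defines it as "beginning with fertilization and ending at birth".
- **How the tp1 stress score is used.** Section 7.2 plans "Analyses (adjusted by baseline value and protocol specified variables) of perceived stress at 37 week gestation". It tests the primary outcome at 5% and adds: "The p values of the remaining four tests will be adjusted using Hommel's procedure".
- **What else rests on tp1.** Trust in coping with birth is measured at tp1 only. Section 6.1 gives the reasoning: "Structured antenatal education may improve women's trust in their ability to cope with birth resulting in e.g. lower epidural rates". Trust in coping at discharge is also tp1 only. The Edinburgh depression score, the anxiety score and breastfeeding intention are collected at tp1 as well.

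No section closes tp1 at birth, stops its reminders after delivery, or says how a later answer is classified. Section 3.6 discontinues only women with a miscarriage or stillbirth. The trial organisation section mentions an IT system for collections at individual time points but gives no closing rule.

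**The concern.** Tp1 has a narrow place in the design: after the antenatal sessions at 25, 33 and 35 weeks, and before birth. The other follow-up questionnaires have months of room around them, so a three-week contact chain does them little harm. At tp1 the same chain ends on or after the expected due date.

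A woman who answers the second reminder or the phone call may already have a newborn. Her stress score then describes the first days of parenthood, and her trust in coping with birth refers to a birth that is over. The secondary outcome would no longer be the antenatal quantity that its name promises, and the mixture would depend on how late women respond. For the trust item the loss is one of meaning more than power, because an answer given after labour can reflect how labour went.

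**Working it through.** **1. Contact dates.** Inputs are tp1 at 37 weeks (section 3.8 and Table 1) and the intervals in section 3.8. Taking 37 weeks as 37+0 and counting the 14 days from the first e-mail:

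| Contact | Arithmetic | Gestational age |
|---|---|---|
| First e-mail | – | 37+0 |
| Reminder 1 | +7 days | 38+0 |
| Reminder 2 | +14 days | 39+0 |
| Phone call | +14 +7 = +21 days | 40+0 |

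If the 14 days run from the first reminder, the call falls at 7 + 14 + 7 = 28 days, that is 41+0.

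**2. How many women have delivered by then.** The protocol gives no birth distribution. Assume a normal distribution with mean 39.5 to 40.2 weeks and SD 1.3 to 1.8 weeks. The three combinations tried put 6 to 16% of women delivered by 38 weeks, 22 to 37% by 39 weeks and 46 to 63% by 40 weeks. These shares describe all women. A woman who answers the first e-mail never enters the reminder chain, so they are not the share of tp1 answers given after birth.

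**3. The plan's own power figure.** Section 7.1 gives 878 per arm, SD 6, difference 1 and alpha 5% (taken as two-sided).

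- SE = 6 × √(2/878) = 0.286
- Power ≈ Φ(1/0.286 − 1.96) = Φ(1.53) = 93.7%, as stated.

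**4. Illustration of the effect on power.** Let f be the share of tp1 answers given after birth; the protocol does not supply it. If these answers are kept and carry no treatment effect, the difference becomes 1 × (1 − f). If they are excluded, the number per arm becomes 878 × (1 − f) and the difference stays at 1.

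| f (assumed) | Kept: difference | Kept: power | Excluded: n per arm | Excluded: power |
|---|---|---|---|---|
| 5% | 0.95 | 91.3% | 834 | 92.6% |
| 10% | 0.90 | 88.2% | 790 | 91.2% |
| 20% | 0.80 | 79.8% | 702 | 87.8% |

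Under this assumption, excluding the late answers costs less power than keeping them. The figures use an unadjusted 5% level, as section 7.1 does.

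**The case against.** **The analysis plan could settle it.** Time windows often sit in a statistical analysis plan, which the protocol announces and which is not at hand. This stands for the rule on classifying late answers. It does not cover the contact chain, which section 3.8 itself fixes. An analysis plan can discard an answer given after birth, but it cannot stop the reminders that solicited it or bring the contacts forward.

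**The wordlist already excludes such answers.** If gestation ends at birth, a delivered woman is not at 37 weeks gestation. That reading is fair, and nothing says that late answers would be filed as tp1. But section 3.8 does not apply the definition, and its reminders run on without regard to delivery.

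**The size is unknown.** This stands in full. The postnatal share has neither a lower nor an upper bound in the protocol. Zero effect after birth is a harsh assumption, because the programme also aims to lower stress then. The Abstract plans 2350 women. With 1175 per arm and full response, the harshest case shown gives SE = 6 × √(2/1175) = 0.248 and Φ(0.80/0.248 − 1.96) ≈ 90%.

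**Stronger readings that a reader might infer.**

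- *That trust in coping with birth is a confirmatory endpoint.* Section 6.1 lists it as an intermediate outcome.
- *That a planned causal analysis from trust to epidural use would be reversed.* Section 7.2 plans no mediation analysis.
- *That the arms would be biased against each other.* The contact rule is identical in both arms, and no difference in response timing can be shown from the protocol.

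**Conclusion.** The point holds as a defect in the contact schedule for one time point. The dates follow directly from section 3.8, and the absence of a closure at birth is plain.

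The main consequence is for perceived stress at 37 weeks, the Perceived Stress Scale analysis that section 7.2 names just before its Hommel rule. The section does not list the four adjusted tests, so membership is read from that context. The tp1 trust items (intermediate) and the tp1 depression and anxiety scores (explorative) are affected in meaning.

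The drop from 93.7% to about 91 to 80% rests on two assumptions outside the protocol: 5 to 20% postnatal answers, and no effect in them. It is illustration, not an estimate. Epidural use comes from the obstetric database and is untouched, as are the Perceived Stress Scale tests at times 2 to 4. This is worth correcting because the correction is small, but it does not threaten the trial's main conclusion.

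**What to change.** Amend section 3.8 for tp1 only:

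1. Stop tp1 reminders and the phone call once a birth is registered.
2. Use a shorter tp1 reminder chain, with intervals for the sponsor to choose, so that most contacts fall well before the due date.
3. Count a tp1 answer as antenatal only if its web time stamp precedes the birth date in the obstetric database. Treat later answers as missing at tp1 for the stress, depression, anxiety and trust items.

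The third rule is needed even with the first, because a birth may be registered after a reminder has gone out. It uses a data source that the trial already holds.

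The cost is more missing tp1 values, and that missingness depends on the date of birth, an event after randomisation. Under section 7.2, more than 5% missing together with a Little's test p below 5% makes multiple imputation the primary analysis, so the rule could trigger that switch. The shorter chain limits this by bringing answers forward. Reporting by arm how many tp1 values are missing because of birth would let readers judge what remains.
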